### Data Management

2.13

Data will be collected onto paper CRFs by a research team member named on trial delegation log. Completed CRFs will be sent next day, tracked and signed for via Royal Mail to York Trials Unit, based at the University of York. No patient identifiable information will be mailed. Data will be entered into a secure REDCap database hosted on the University of York cloud‐based server by a data imputer and checked by a second data imputer. All data queries will be raised with the research team.

The paper trial file, incomplete CRFs and participant consent forms will be stored in locked filing cabinets in the research office at Hull University Teaching Hospitals NHS Trust, accessible only by swipe card access.

Digital data, including screening logs, audio recordings, patient letters, transcripts and DFU photographs will be stored in the electronic trial file only accessible by the trial researchers. The digital trial file will be held on the NHS Trust server, which is secured with firewalls and antivirus software. Only researchers on the delegation log will have access to the electronic trial file.

### Statistical Analysis

2.14

Eligibility and recruitment rates will be reported for the entire population screened. Intervention adherence, crossover, follow‐up and missing data will be reported for each arm and in total. The progression of participants through the trial will be illustrated with a flow diagram. Reasons for ineligibility, non‐consent, non‐compliance and drop‐out will be reported.

Baseline characteristics will be summarised by arm and in total for randomised participants. Continuous outcomes will be reported as means, standard deviations, medians and interquartile ranges. Categorical data will be reported as counts and percentages.

Secondary outcomes will be reported descriptively at each follow‐up time point for each trial arm. No statistical testing will be undertaken as this is a pilot trial, however between group differences will be presented with associated confidence intervals and illustrated in appropriate graphs (e.g., Kaplan–Meier plots). All comparisons will follow intention‐to‐treat principles.

The number of adverse events will be reported by type and severity for each arm and overall. Events will be summarised as total event rate and mean/median number of events per patient in each arm.

Data will be analysed using Microsoft Excel (2021; WA, USA), IMB SPSS (version 28.0.0.0; Armonk, NY, USA) and STATA (Version 18; TX, USA).

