### Interventions

2.5

The pilot RCT will compare high dose, low dose and sham ESWT. High dose ESWT is 500 shocks/cm^2^ and low dose ESWT is 100 shocks/cm^2^. A minimum of 500 shocks will be administered in the high dose arm and a minimum of 100 shocks will be delivered in the low dose arm. The number of shocks in the active arms is based on the current literature [25].

ESWT will be delivered using a PiezoWave^2^ device (Richard Wolfe, Germany) by a trained researcher. The machine will deliver shockwaves at 0.1 mJ/mm^2^ at 5 Hz and penetrate 5 mm. The DFU will be undressed, cleansed with Prontosan(B Braun, UK) and sharp debrided if required (local standard of care). The DFU will then be covered with a clear film and ultrasound gel applied to the ESWT paddle. Care will be made to ensure there are no air bubbles between the ESWT paddle and film and the ulcer bed.

Sham ESWT will be simulated using a 6 min and 30 s audio‐recording of ESWT. A speaker with the audio‐recording of ESWT will be attached to the top of the ESWT machine. The DFU and ESWT machine will be prepared in the same way as the active arms. Instead of pressing the button to begin delivering shockwaves, the play button on the speaker will be pressed to start the recording. The ESWT paddle will be held onto the ulcer for the duration of the recording. This has been a successful method of blinding in other RCTs of ESWT [29].

High dose, low dose and sham ESWT will be delivered three times over a 7 ± 2 days period. This time interval was chosen to coincide with the standard practice of a dressing change once every 3 days. The treatment will be stopped if the patient is unable to tolerate ESWT.

The decision to investigate the dose of ESWT based on varying the number of shockwaves per cm^2^, as opposed to the frequency of sessions, was on the advice of the PPI group. The PPI group felt longer but fewer sessions of ESWT was more acceptable while the effectiveness of ESWT remains unclear. This is because people with DFUs tend to have many healthcare appointments and increasing the burden of appointments may deter some patients from partaking. In addition, a recent systematic review did not find any differences in healing times between number of ESWT sessions or number of shockwaves delivered [25].

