### Data Collection

2.12

Data items for collection are based on international reporting standards for DFU studies [41]. Data will be collected from the patient, electronic patient records or direct patient measurements and entered onto a paper case report form (CRF) (Table 2).

**TABLE 2 iwj70176-tbl-0002:** Sources of data.

	Patient reported	Medical records	Direct measurements/observation
Enrolment			
Eligibility log			X
Recruitment log			X
Informed consent			X
Allocation			X
Deliverability			
Adherence to treatment			X
Adherence to follow up			X
Intervention			
Treatment completed			X
Number of shockwaves			X
Time to deliver ESWT			X
Side effects of ESWT	X		X
Demographics			
Age	X		
Sex	X		
Ethnicity	X		
BMI	X	X	X
Smoking status	X		
Weekly alcohol intake	X		
Type of diabetes mellitus	X	X	
HbA1c		X	
Diabetes management	X	X	
Cardiovascular disease	X	X	
Respiratory disease	X	X	
Chronic kidney disease	X	X	
Surgical history	X	X	
Allergies	X	X	
Medications	X	X	
Antibiotic use	X	X	
Ulcer characteristics			
Site			X
Laterality			X
Ulcer age	X	X	
SINBAD score			X
WIfI stage			X
Foot deformity			X
DFU photograph			X
Area			X
Depth			X
ABPI			X
Absolute toe pressure			X
Time to assess DFU			X
Ulcer care			
Dressing(s) type	X	X	X
Offloading footwear	X	X	X
Sharp debridement	X	X	X
Other interventions	X	X	X
Quality of life			
EQ‐5D‐3L	X		
DFS‐SF	X		
Wound‐Qol‐14	X		
Healthcare use^a^			
Number of outpatient appointments	X	X	
Number of GP appointments	X	X	
Number of hospital admissions	X	X	
Length of stay	X	X	
Number of practice nurse appointments	X	X	
Number of district nurse appointments	X	X	
Number of podiatrist appointments	X	X	
Number of prescriptions	X	X	
Number of operations	X	X	
Ulcer healing			X
Adverse events	X	X	X
Qualitative interview	X		

Abbreviations: ABPI: ankle brachial pressure index; BMI: body mass index; DFS‐SF: diabetic foot ulcer scale—short form; DFU: diabetic foot ulcer; EQ5D5L: EuroQol 5‐dimensions 5‐levels; ESWT: extracorporeal shockwave therapy; GP: general practitioner; INBAD: site ischaemia neuropathy bacterial infection area and depth score; WIfI: wound ischaemia foot infection stage.

^a^
Taken from the patient healthcare resource use diary.

Data relating to participant demographics, the DFU, standard care and quality of life will be taken at baseline.

Data relating to the number of shockwaves delivered, time to deliver ESWT and side effects will be recorded at each intervention session.

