### Harms

2.17

All side effects will be recorded during the pilot RCT. The expected transient side effects of ESWT are mild pain, burning sensation, itchiness and erythema around the ulcer. The standard definitions of adverse event (AE), serious adverse event (SAE), unexpected and related will be used [51]. All AEs and device failures will be recorded. All SAEs will be reported to the Principal Investigator (PI) within 24 h of the event occurring. The PI will report SAEs to the Sponsor and Research Ethics Committee (REC), following Health Research Authority (HRA) guidance.

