## Discussion

4

This protocol outlines the study design for a pilot RCT evaluating ESWT for DFU healing and a qualitative study. Findings from a recent systematic review reported promising results with ESWT for DFU healing, but low certainty in evidence on the effectiveness and unclear impact of dosing restricted recommendations that ESWT should become part of routine care [25]. Certainty in the data was often downgraded due to imprecision, indirectness and risk of bias. Specific areas of concern were the randomisation process, (non‐)blinding of participants and outcomes assessors, and outcome reporting. This pilot RCT aims to address these areas and ensure methods used will provide reliable results in a definitive RCT.

The NIHR view pilot RCTs as value for money when they answer key uncertainties in trial conduct [54]. In this trial, relevant uncertainties include number of eligible patients, patient willingness to participate, adherence to the treatment arms and whether it is possible to collect the relevant outcome data using the methods described. Identifying problems with recruitment, delivery of the intervention and collection of outcomes measures in the pilot RCT allows for these processes to be refined for the definitive trial and minimises the chances of wasting research resources by proceeding straight to a definitive trial that is not fit for purpose. The failure of trial methods in this pilot RCT is an outcome, not a detriment to the evidence generated. In addition, knowledge of the expected numbers of participants to engage allows for logistics to be planned, for example how many trial sites will be needed and the expected time to recruit the sample size. This will inform the funding application for a definitive trial.

When compared to other trials of ESWT in DFU, the eligibility criteria in this pilot RCT slightly differs as it includes participants with neuro‐ischaemic and infected DFUs [55, 56, 57, 58, 59, 60]. The rationale in ESWT is hypothesised to stimulate angiogenesis and increase eradication of bacteria in the presence of antibiotics. Including these participants in the pilot RCT will explore whether ESWT is safe (judged by numbers of SAEs) and number of participants with these ulcer characteristics. This will inform statistical and sample size planning in the definitive trial to explore the effectiveness of ESWT in these patient groups.

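### The planned adverse event summary counts events and never participants affected, so if session side effects count as adverse events, early stopping can lower an arm's total and mean

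*Protocol article*

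**What the plan says.** Section 2.14 (Statistical Analysis) names two harm summaries. The first is a tabulation: "The number of adverse events will be reported by type and severity for each arm and overall". The second is per arm: "Events will be summarised as total event rate and mean/median number of events per patient in each arm". Every one of these measures counts events. The denominator of the total event rate is not given.

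Three other statements bear on how the counts arise:

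- Section 2.5 (Interventions) sets three sessions in every arm: "High dose, low dose and sham ESWT will be delivered three times over a 7 ± 2 days period". It adds: "The treatment will be stopped if the patient is unable to tolerate ESWT".
- Section 2.12 (Data Collection) has side effects noted session by session: "Data relating to the number of shockwaves delivered, time to deliver ESWT and side effects will be recorded at each intervention session".
- Section 2.17 (Harms) lists what is expected: "The expected transient side effects of ESWT are mild pain, burning sensation, itchiness and erythema around the ulcer".

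Tables 2 and 3 carry side effects of ESWT and adverse events as separate rows. Section 2.14 names only adverse events. Section 2.6 (Outcomes) lists adverse events as a secondary outcome, and section 2.14 already promises between-group differences with confidence intervals for secondary outcomes.

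**The concern.** The expected side effects are transient and tied to the session, so one participant can contribute up to three events of the same type. A participant who stops after the first session can contribute only one. The harm itself can therefore remove later chances of being counted. Two arms can then be ranked by how many sessions were tolerated, and not by how many people were affected.

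The three arms exist to explore dosing, and the harm table is one of the things the pilot hands to the definitive trial. The designers of that trial will want the share of participants affected in each arm. Event totals and means do not supply it: 30 events of one type in an arm of 30, with at most three per participant, fit anything from 10 to 30 participants affected. The Discussion also frames safety as a count, in its aim to "explore whether ESWT is safe (judged by numbers of SAEs").

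**Working it through.** **Arm size.** The article's own calculation is 23 × 3 = 69; 69 × 0.3 = 20.7, taken as 21; 69 + 21 = 90. With 1:1:1 allocation (section 2.10), 90 / 3 = 30 per arm. The article states no expected event rates, so all event patterns below are assumed.

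**Conditions.** Session side effects are counted as adverse events, and stopping for intolerance ends the course. The article settles neither.

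**Worked example, one event type, 30 per arm.** In arm A, 14 participants have an event at session 1 and stop; the other 16 complete three sessions. In arm B, 6 participants have an event at all three sessions, and all 30 complete.

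| Measure | Arm A | Arm B | Arm that looks worse |
|---|---|---|---|
| Total events (planned) | 14 × 1 = 14 | 6 × 3 = 18 | B |
| Mean per patient (planned) | 14/30 = 0.47 | 18/30 = 0.60 | B |
| Median per patient (planned) | 0 | 0 | neither |
| Participants with at least one event | 14/30 = 47% | 6/30 = 20% | A |
| Sessions delivered | 14 × 1 + 16 × 3 = 62 | 30 × 3 = 90 | – |
| Events per session delivered | 14/62 = 0.23 | 18/90 = 0.20 | A |

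**Is the pattern special?** Let p be the per-session risk in an arm where the first event ends treatment, and q the risk in an arm where treatment continues, with sessions independent. Expected events per patient are 1 − (1 − p)³ in the first arm and 3q in the second. At equal risk the share with at least one event is the same in both arms, 1 − (1 − p)³, but the stopping arm has the lower mean:

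| p = q | Stopping arm, mean | Continuing arm, mean |
|---|---|---|
| 0.1 | 0.271 | 0.300 |
| 0.2 | 0.488 | 0.600 |
| 0.3 | 0.657 | 0.900 |
| 0.5 | 0.875 | 1.500 |

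Setting 1 − (1 − p)³ = 3q gives the risk at which the stopping arm's mean catches up: p = 0.263 for q = 0.2, and p = 0.536 for q = 0.3. For q of 1/3 or more the stopping arm can never show the higher mean.

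**How often would the totals mislead?** Simulation with 30 per arm under the same model gives the chance that the stopping arm has fewer events although its true risk is higher: 51% for p = 0.25 v q = 0.20, 31% for 0.30 v 0.20, and 73% for 0.40 v 0.30. Reversal is plausible but not certain.

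**Does the median help?** Only when at least half of an arm is affected. With 15 of 30 having one event the median is 0.5, and with 17 of 30 it is 1. Below half it is 0 in either arm and says nothing.

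**The case against.** Much can be said for the plan as written.

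- **Intolerance is reported elsewhere.** Section 2.14 gives intervention adherence by arm, reasons for non-compliance and drop-out, and a flow diagram. Completing three sessions is part of the primary outcome. In the example, arm A would show 16/30 = 53% adherence with reasons, against 100% in arm B. A reader might infer that the pilot report as a whole would present a badly tolerated arm as the safer one. The article does not support that; only the harm summary, read alone, can mislead.
- **Counts are split by type and severity.** If the events that end treatment are graded higher, the table would separate them from mild repeated ones. This softens the distortion, but the cells remain event counts.
- **The median can flag the worse arm**, once half or more are affected. This limits the problem to lower frequencies.
- **The mechanism is conditional.** If session side effects are not adverse events, the three-session counting does not touch the quoted sentence. In that case the article names no summary for the side-effect item. Either way a sentence is needed. Likewise, the stopping sentence could refer to the session or to the course.
- **Dose.** A reader might also infer that a dose-related harm would be reversed. The article nowhere says that these effects depend on dose, so that reading falls.
- **Level of detail.** An extra column is often left to an analysis plan. Here, however, the article itself names the measures, and those it names omit participants affected. The line on reporting categorical data as counts and percentages sits with the baseline summaries and does not commit to it.

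The Stop/Go criteria in section 2.16 use recruitment, adherence, follow-up and related serious adverse events, so no pilot decision turns on this point.

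**Conclusion.** The point holds in a limited form. The stated harm measures give no number of participants affected and leave the rate's denominator open. If session side effects count as adverse events and stopping ends the course, totals and means fall when participants stop early. They can then rank two arms in the opposite order to participants affected: in the assumed example, 14 v 18 events against 47% v 20% of participants. The effect is confined to session-related events in the treatment period of 7 ± 2 days, and to the harm summary. A rate per session delivered would largely correct it, but none is specified. The event patterns are assumptions, since the article gives no rates. Severity is minor.

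**What to change.** In section 2.14, add for each arm the number and percentage of participants with at least one event, by type and maximum severity. Do this for adverse events and for the session side-effect item, and state whether the latter count as adverse events. Give between-arm differences with confidence intervals, as already planned for secondary outcomes. Define the denominator of the event rate, using sessions delivered for session side effects. Keep the event totals alongside, because participant percentages do not show repeat events. State also whether the stopping sentence in section 2.5 refers to the session or to the course, so that sessions delivered can be counted consistently; no clinical rule needs to change for this analysis.

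The cost is a sentence or two and one extra table. Section 2.12 and Table 3 already provide for side effects, treatment completion and adverse events to be recorded at each session, so no new data are needed.

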### Data Monitoring

2.16

Eligibility rates, recruitment rates, treatment adherence, follow‐up adherence and adverse events will be reviewed by the trial management group (TMG) monthly and the trial steering committee (TSC) bi‐annually. The TSC will use Stop/Go criteria to decide whether to continue the pilot trial or pause recruitment and amend trial processes. The Stop/Go criteria [50] are:
–Green (continue): > 60% recruitment, adherence to treatment arm and follow‐up attendance per month.–Amber (continue, review trial processes): 30%–60% recruitment, adherence to treatment arm and follow‐up attendance per month.–Red
○< 30% (Stop, amend trial processes) recruitment, adherence to treatment arm and follow‐up attendance per month.○Serious adverse events related to ESWT (stop, review).

The auditing of the trial processes will take place by independent auditors from the Sponsor's Research, Development and Innovation (RD&I) Department.

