### Sample Size

2.8

The pilot RCT aims to recruit 90 participants overall. This figure is based on the minimum recommended number of trial participants required to estimate the standard deviation to inform a sample size calculation for a definitive trial [32, 33, 34, 35, 36].

Sample size calculation: 23*3 = 69 minimum number of participants*number of arms.

69*0.3% = 21 30% estimated attrition.

69 + 21 = 90.

The qualitative study sample size is informed by informational power, whereby the more information a sample holds, the smaller the sample needs to be [37, 38]. The aim of this study is narrow and each participant will hold experience relevant to the aim of the study. The researcher undertaking the interviews has experience in DFU, treatments and prior experience of interviewing. The combination of patient and researcher experience is likely to result in more in‐depth data exploration, resulting in fewer participants needed. The qualitative study aims to recruit 36 participants in total split between the following groups:
–Complete the trial: 12–Drop‐out of the trip: 6–Decline trial participation: 6–DFU MDT clinicians: 12

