### Recruitment

2.9

All pilot RCT participants will be recruited from one tertiary care hospital from the inpatient and outpatient services, with links to the community diabetic foot services. The National Institute of Health and Social Care Research (NIHR) Clinical Research Network will also support recruitment to the study through their contacts with local general practice and community services (study reference CPMS: 52540). The trial will recruit patients over an 18 months recruitment period.

Potential participants will be approached by the research team after discussion with the clinical team and provided a patient information sheet (PIS). This will be followed by a telephone call within the subsequent 7 days to allow patients time to read and understand the information. If a researcher is not available, the clinician can provide the patient with a PIS and complete a consent to contact form.

A log of all screened patients will be kept to document reasons screened patients were not eligible and eligible patients did not enter the study. This will be used to monitor for under‐representation of under‐served groups and identify barriers to entering the trial.

Qualitative study participants will be recruited from the same patient pool as the pilot RCT participants. Purposeful sampling will be used to recruit participants with varying demographics (gender, age, ethnicity), treatment allocation and wound severity (based on Wound Ischaemia, foot Infection stage). Patients will either be approached at a F2F appointment or invited via the telephone. Clinicians will be recruited nationally using purposeful sampling to ensure variation based on the healthcare professional group, location in the United Kingdom and type of healthcare setting. They will be identified at national conferences, through the Vascular Society Diabetic Foot Specialist Interest Group, X (formally Twitter) and snowballing. Clinicians will be approached in person or via email. All potential participants will be provided with a PIS. A log will be kept of all screened patients and clinicians to record reasons they were ineligible or declined participation.

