### Allocation

2.10

Participants will be randomised on a 1:1:1 allocation ratio to sham ESWT, low dose ESWT and high dose ESWT. Participants will be stratified by ulcer size (< 1 and ≥ 1 cm^2^) and ischaemia (ABPI 0.7–0.79 and ≥ 0.8; OR absolute toe pressure 50–59 and ≥ 60 mmHg). These two factors are predictive of healing [39, 40]. Stratified block randomisation with randomly varying block sizes of 3 and 6 will be used. Randomisation will be performed using an online randomised tool hosted at York Randomisation Service, York Trials Unit. The site researcher will enter the participants details into the online tool. The York Trials Unit trial manager, Principal Investigator and the site researcher will then receive an email with the participant's trial arm allocation.

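### The Green boundary for follow-up (above 60%) is below the 70% retention that the sample size plans on, so worse-than-planned attrition does not trigger the Amber review

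*Protocol article*

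**What the plan says.** **Sample size (Section 2.8).** The target of 90 rests on the "minimum recommended number of trial participants required to estimate the standard deviation to inform a sample size calculation for a definitive trial". The calculation starts from "23*3 = 69 minimum number of participants*number of arms", adds an allowance written as "69*0.3% = 21 30% estimated attrition", and sums the two to 90. Allocation is equal (Section 2.10: "Participants will be randomised on a 1:1:1 allocation ratio"), so 90 means 30 per arm.

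**Monitoring (Section 2.16).** The trial steering committee uses Stop/Go bands to "decide whether to continue the pilot trial or pause recruitment and amend trial processes". The top band is "Green (continue): > 60% recruitment, adherence to treatment arm", and the line goes on to include follow-up attendance, all expressed per month. The next band, "Amber (continue, review trial processes", covers 30% to 60%. Red is below 30%. Separately from the bands, the trial management group reviews the rates every month and the steering committee twice a year.

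**Definition of follow-up adherence (Section 2.6).** The numerator is participants who attend every follow-up visit. The denominator is all participants in the trial.

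Nothing in the article links the 60% boundary to the 30% attrition allowance or to the minimum of 69.

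**The concern.** The bands and the sample size both state how much loss to follow-up the trial can bear, and they disagree. The sample size allows for 30% loss; Green accepts anything short of 40%. Only Amber carries an explicit instruction to review trial processes, so the gap between the two figures is a range in which the trial does worse than planned and the rule still says continue.

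At stake is the stated purpose of the sample size, a usable SD for planning the definitive trial. Deliverability, including adherence to follow-up, is the primary objective, and these bands are the only decision rule that the article attaches to it. The early signal should therefore be set where the plan begins to fail.

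**Working it through.** **Inputs.** From Section 2.8: minimum 23 per arm, 3 arms, 30% attrition, total 90. From Section 2.10: 1:1:1 allocation. From Section 2.16: Green above 60%, Amber 30–60%.

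**1. Reproduce the plan's figure.** 23 × 3 = 69. 69 × 0.30 = 20.7, rounded to 21. 69 + 21 = 90. The printed 0.3% must be a slip for 0.3 or 30%, because 69 × 0.003 = 0.2.

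**2. Retention implied by Section 2.8.**
- Assumed: 100% − 30% = 70%. Completers: 90 × 0.70 = 63, or 21 per arm.
- Needed for the stated minimum: 69 / 90 = 76.7%.

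The two differ because attrition was added as 30% of 69. Dividing instead gives 69 / 0.70 = 98.6, that is 99. This is a separate slip in Section 2.8.

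**3. Numbers attending at different rates, out of 90.**

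| Attendance | Band | Attending | Per arm |
|---|---|---|---|
| 60% | Amber (top) | 54.0 | 18.0 |
| 61% | Green | 54.9 | 18.3 |
| 65% | Green | 58.5 | 19.5 |
| 69% | Green | 62.1 | 20.7 |
| 70% (plan) | Green | 63.0 | 21.0 |
| 76.7% | Green | 69.0 | 23.0 |

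The band labels concern follow-up only and take recruitment and treatment adherence to be Green as well. From 61% to 69%, follow-up is Green but below the plan's own 70%. At 61%, about 55 attend, 14 short of 69.

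**4. Chance of reaching 69 of 90 (exact binomial).** With true attendance of 61% it is about 0.1%. At the planned 70% it is about 10%.

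**5. Effect on the SD.** The upper 95% limit factor is √(df / χ²₀.₀₂₅,df). For a per-arm SD, df = n − 1:
- n = 23: 1.42
- n = 21: 1.44
- n = 18: 1.50

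For an SD pooled over three arms, df = N − 3:
- N = 69: 1.21
- N = 63: 1.22
- N = 55: 1.24

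**6. Is the monthly rate the same thing as retention?** Not exactly, and the direction depends on the reading. Assume three face-to-face visits, equal rates and independent misses.
- If 61% is attendance at each visit, the share attending all three is 0.61³ = 23%, while each visit still has about 55 of 90.
- If 61% is the share attending all three (the Section 2.6 definition), attendance per visit is 0.61^(1/3) = 85%, about 76 of 90, which exceeds 69.

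The figure of 55 therefore holds only if 61% applies at the visit that supplies the SD. Section 2.8 names neither that visit nor the outcome.

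**The case against.** The strongest reply is that the two sections measure different things. Section 2.16 gives a monthly rate for steering a running pilot, whereas the 30% in Section 2.8 is attrition over the whole trial. This stands as a limit on the size of the problem: step 6 shows that one reading leaves enough attenders. It does not reconcile the figures, because the article does not say which reading applies and the two allowances for loss still differ.

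Second, attendance is not the same as having data. Section 2.12 provides for routine medical records when a participant is lost, and Table 3 adds telephone follow-up and healed-ulcer visits. Healing may well be known for people who do not attend. This also stands. What remains exposed is measured ulcer size and, to a degree, the quality-of-life questionnaires.

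Third, the placing of traffic-light boundaries is partly judgement, and Section 2.16 cites a source for its bands that cannot be seen here. That is fair, but a boundary looser than the trial's own attrition allowance needs a reason, and none is given.

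A reader might go further than the documents allow in four ways:
- **That problems go unreviewed under Green.** Section 2.16 has the trial management group look at the rates monthly whatever the band. What is missing is the formal Amber trigger.
- **That Green should start at 77%.** That figure comes from the additive inflation in Section 2.8, and it would put the plan's own 70% into Amber.
- **That the recruitment threshold fails in the same way.** Section 2.9 says "The trial will recruit patients over an 18 months recruitment period", but no monthly target is stated. Dividing 90 by 18 to get 5 per month is a reader's construction. Multiplying shortfalls on that basis (90 × 0.61 × 0.61, about 33 completers) has no footing in the text.
- **That these are progression criteria.** They govern whether the pilot continues, not whether a definitive trial follows.

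**Conclusion.** The inconsistency is real and its consequence is modest. Green begins just above 60%, while the sample size plans on 70% and needs 76.7% for its stated minimum. Follow-up of 61–69% is worse than planned without triggering the Amber review.

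If that range held at the visit supplying the SD, the trial would have about 55–62 attenders instead of the 63 that its assumption yields or the 69 that it states. The worst case in that range raises the upper limit factor for a per-arm SD from 1.42 to about 1.50, and a pooled SD would lose less. This rests on two assumptions: that attendance at that visit stands in for retention, and that the outcome in question needs attendance. It does not undermine the descriptive reporting of deliverability.

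The range from 70% to 76.7% is also Green with fewer than 69 attending, but that part comes from the arithmetic in Section 2.8, not from the bands.

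**What to change.** 1. **Section 2.16.** Set Green for follow-up at 70% or above and Amber from 30% to below 70%, and leave Red unchanged. Assess the rate on cumulative attendance at the visit that supplies the SD, and name that visit.
2. **Section 2.8.** State that 90 recruits at 30% attrition yield 63 completers (21 per arm), not 69, and correct the printed 0.3%.

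Both are changes of wording. The cost is more process reviews in the Amber band: a trial running exactly at its planned 70% sits on the boundary, so chance alone will put it in Amber at some reviews. Using a cumulative rate limits this, because monthly counts are small (90 × 3 = 270 face-to-face visits due over 18 months of recruitment plus 24 weeks, roughly 11 a month). As Amber means continue, nothing stops earlier than it would now.
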